#### Neural factors

Other predictors of cognitive variability we consider are brain structure and function. With respect to structure, it has been shown that individual differences in cognitive variability are linked to differences in white matter microstructure [49, 68] and that a reduction in cognitive variability over time relates to the development of white matter microstructure [69]. Specifically, the neural noise hypothesis states that myelination of axons leads to less noisy transmission of brain signals, and ultimately less behavioural variability [70].

Apart from brain structure, individual differences in cognitive variability have also been linked to variability in brain function (i.e., neural variability; [17, 71–74]. One interpretation of neural variability is that it reflects neural noise which affects our ability to parse weak and ambiguous signals, directly *causing* cognitive variability [75, 76]. In contrast, when using functional magnetic resonance imaging (fMRI), neural variability, measured through the blood oxygen level-dependent (BOLD) signal (with higher BOLD signal indexing lower neural noise), has been associated with better cognitive performance, as well as lower variability in performance [77]. A different interpretation of fMRI-based BOLD variability is that it reflects the dynamic range of a person’s brain, with higher variability reflecting the ability to occupy a greater range of states (e.g., alert, on-task, relaxed) and readily respond to changing environments. This interpretation is supported by studies linking greater functional connectivity with higher neural variability to meet increasing task complexity [74]. Neural variability may index both neural noise and the ability to switch between states, as these are features that can be modulated by the excitation-inhibition balance, which refers to the balance between excitatory (promoting neural activity) and inhibitory (reducing neural activity) neural signals [78].

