**Fig. 8 Fig8:**
[figure not shown]
Deep phenotyping procedure. The deep phenotyping (the first and third year of the study) includes MRI (structural, functional, diffusion), and eye-tracking (pupillometry, gaze). Additionally, children and their parents perform cognitive tasks and a set of questionnaires

The tasks are explained and practised in the mock scanner prior to the actual MRI scan. The order of the task blocks during the scan (high or low time constraints) are randomised.

Outside of the MRI scanner, children perform each of the five cognitive tasks for 3 min (15 min total). Children also respond to a short set of questionnaires (~15 min). While children are in the scanner, parents or guardians (if they also provide consent themselves) also respond to a set of questionnaires and perform the cognitive tasks on a tablet.

Details of the sequences of the MRI scan can be found in Table 1. The MRI scan consists of:MPRage and Sparse MP2rage: gold standard structural scans. MP2-Rage [108] allows for greater specificity of myelination, one of the core research questions.Naturalistic viewing fMRI: participants will watch a short video clip (~8 min), featuring a social scene from an age-appropriate, mainstream movie (Despicable Me).Task 1, fMRI (including eye-tracking/pupil dilation): a fluid reasoning task familiar to the children from the cognitive task battery, but with an additional condition of low or high time constraints.Task 2, fMRI (including eye-tracking/pupil dilation): fluid reasoning task with the opposite condition (low or high time constraints) compared to the first task block.Diffusion weighted imaging: this diffusion weighted sequence balances a realistic acquisition time with high quality imaging data.

**Table 1 Tab1:** MRI sequences used in CODEC-MRI

Scan type	Sequence	TR (ms)	TE (ms)	Flip angle (°)	FOV (mm)	Voxel size (mm)	Other	Task
T1-weighted	MPRAGE	2300	3.03	8	256 × 256 × 192	1 × 1 × 1	GRAPPA: 2; TI: 1100 ms	None
T1-weighted	Sparse MP2RAGE	5000	2.88	Angle 1: 4 Angle 2: 5	240 × 256 × 224	1 × 1 × 1	TI 1: 700 (ms) TI 2: 2500 (ms)	None
Resting-state fMRI	EPI	1500	TE 1: 12.40 TE 2: 34.30 TE 3: 56.20	75	210 x 210 x 128	2.5 × 2.5x2.5	GRAPPA: 2; Volumes (N): 350; Slices: 51; Slice thickness: 2.5 (mm)	Movie watching
Task fMRI -Matrix reasoning task	EPI	1500	TE 1: 12.40 TE 2: 34.30 TE 3: 56.20	75	210 x 210 x 128	2.5 × 2.5x2.5	GRAPPA: 2; Volumes (N): 350; Slices: 51; Slice thickness: 2.5 (mm);	Visual stimuli and manual response

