**Aim (2) Underlying mechanisms:** in the imaging arm, we consequently use key predictors of interest in the deeply phenotyped subsample (*N* = 200) to test mechanistic hypotheses about the (hypothesised) causes of individual differences in variability. In terms of brain structure, we first test the known association between larger grey matter volume and better cognitive performance to replicate previous findings [124]. Then, we test the neural noise hypothesis, which suggests that better myelination of the brain is associated with less variability due to decreased signal loss [73].*Hypothesis 2.1: Children with larger grey matter volume will demonstrate better cognitive performance in the behavioural tasks.**Hypothesis 2.2: Children with larger white matter volume (better myelination) will demonstrate higher BOLD signal variability (potentially reflecting lower neural noise).**Hypothesis 2.3: Children with higher tract-based indirect measures of myelination (both in white matter tracts and in grey matter) between frontoparietal executive systems (specifically: the SLF, ATR, IFOF and Forceps Minor) will show less variability. This effect will manifest most strongly for complex tasks, as those are most dependent on multi-region information integration.**Hypothesis 2.4: Myelination increases during childhood. Children with steeper increase in myelination (both in white matter tracts and in grey matter) will show sharper decrease in behavioural variability between year 1 (*~*8 years old) and year 3 (*~*10 years old).*

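### Hypothesis 2.2 tests white matter volume but labels it better myelination, so its result cannot be read as a myelination effect

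*Protocol article*

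**What the plan says.** All places are in the Protocol article.

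- **Key hypotheses, Aim 2, introduction to the brain-structure hypotheses:** "we test the neural noise hypothesis, which suggests that better myelination of the brain is associated with less variability due to decreased signal loss".
- **Hypothesis 2.2:** "Children with larger white matter volume (better myelination) will demonstrate higher BOLD signal variability (potentially reflecting lower neural noise". The predictor is a volume, the outcome is BOLD variability, and the bracket equates the volume with myelination.
- **Hypothesis 2.3:** "Children with higher tract-based indirect measures of myelination (both in white matter tracts and in grey matter) between frontoparietal executive systems" are predicted to show less variability, most strongly on complex tasks.
- **Hypothesis 2.4:** "Children with steeper increase in myelination (both in white matter tracts and in grey matter" are predicted to show a sharper fall in behavioural variability.
- **Neural factors:** the background reports that "individual differences in cognitive variability are linked to differences in white matter microstructure" and states the neural noise hypothesis in terms of axonal myelination.
- **CODEC-MRI: imaging procedure:** MP2RAGE is included because it "allows for greater specificity of myelination, one of the core research questions". Of the diffusion scan the article says only that "this diffusion weighted sequence balances a realistic acquisition time with high quality imaging data".
- **Sample size considerations, Imaging arm:** the planning effect is 0.34, between Fractional Anisotropy and variability. It is not a volume effect.

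**The concern.** Volume says how much white matter there is; myelination is a property of that tissue. Two children with equally myelinated white matter can differ in volume simply because one has a larger brain. The bracket in Hypothesis 2.2 therefore fixes an interpretation that its predictor cannot carry.

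This matters because of where the hypothesis sits. The neural noise account runs from myelination, through neural noise, to behaviour. Hypotheses 2.3 and 2.4 relate myelination to behaviour, and Hypothesis 2.6 relates BOLD variability to behaviour. Only Hypothesis 2.2 relates brain structure to BOLD variability. If it is reported under its present label, a volume association could be published as evidence that myelination reduces neural noise, or a null volume result as evidence against it, although that link was not tested with a myelination measure.

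**Working it through.** **1. Predictors and outcomes side by side**

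| Hypothesis | Predictor | Outcome |
|---|---|---|
| 2.2 | White matter volume, labelled better myelination | BOLD variability |
| 2.3 | Tract-based indirect myelination measures, white and grey matter | Variability, read as behavioural because the text ties it to task complexity |
| 2.4 | Change in myelination, white matter tracts and grey matter | Change in behavioural variability |
| 2.6 | BOLD variability | Behavioural performance and its variability |

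Only row 2.2 joins a structural predictor to BOLD variability, and it alone of the three structural rows uses a volume. Hypothesis 2.3 calls its own tract measures indirect, whereas 2.2 gives a coarser measure an unqualified label.

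**2. The plan's own power figures**

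Inputs: N = 200, with power above 80% at r = 0.2 and above 99% at r = 0.3 (Imaging arm). The article states no alpha; two-sided 0.05 is assumed. Fisher z approximation: power ≈ Φ(atanh(r)·√(N − 3) − 1.96), with √197 = 14.04.

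- r = 0.2: Φ(0.2027 × 14.04 − 1.96) = Φ(0.886) = 81.2%
- r = 0.3: Φ(0.3095 × 14.04 − 1.96) = Φ(2.384) = 99.1%

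Both stated figures reproduce. The point disputes neither.

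**3. What a weak proxy could do (illustration only)**

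Assume that true myelination correlates 0.34 with BOLD variability, and that volume correlates v with myelination and is related to BOLD variability only through it. The 0.34 is borrowed from the article's Fractional Anisotropy figure, which concerns a different predictor and outcome. The documents give no v. The observable correlation is then 0.34 × v.

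| v (assumed) | 0.34 × v | Power, N = 200 |
|---|---|---|
| 0.8 | 0.272 | 97.5% |
| 0.6 | 0.204 | 82.7% |
| 0.4 | 0.136 | 48.4% |
| 0.3 | 0.102 | 30.1% |

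In the other direction, assume no myelination effect, a correlation of 0.8 between volume and head size, a correlation of 0.1 to 0.3 between head size and BOLD variability, and no other link. Volume then correlates 0.8 × 0.1 = 0.08 to 0.8 × 0.3 = 0.24 with BOLD variability, and an unadjusted test would be significant in 20% to 93% of studies.

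These ranges show that either error is possible. They do not estimate its size in this study.

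**The case against.** The strongest defence is that the bracket is loose shorthand, that 2.2 is a hedged side prediction (lower neural noise is only potentially reflected), and that the neural noise account, which the article frames as myelination going with less variability, is tested with myelination measures in 2.3 and 2.4. On this view the trouble is one of wording, in one of 23 predictions. Replacing the predictor would also create a different hypothesis, registered after a set that was written before data collection.

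Part of this stands. The account as a whole does not depend on 2.2, and the preregistered volume test should not be discarded. But the listed hypotheses are the preregistered predictions: the named predictor is what will be tested and the bracket is how it will be read. The two do not match.

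A reader might also infer more than the documents support:

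- **That the myelination scans go unused.** This is true of 2.2 only. Hypotheses 2.3 and 2.4 plausibly use them, although the article names no sequence there.
- **That the diffusion scan was acquired for myelination.** The article ties only MP2RAGE to that purpose.
- **That head-size adjustment has been wrongly omitted.** Covariates may be set in the preregistration or analysis plan, which are not shown, so silence in a condensed article is no finding. That volume scales with head size is a general methodological point, used here only to explain why the label fails.
- **That Hypothesis 2.1 has the same fault.** It predicts a grey matter volume association and makes no myelination claim.
- **That disagreement between 2.2 and 2.3 would be due to their predictors.** Their outcomes differ as well.

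**Conclusion.** The concern holds as a stated mismatch between predictor and construct in Hypothesis 2.2. A positive result would support an association with white matter volume, not with myelination; a null result would not count against the step from myelination to neural noise. The conclusion needs only the article's own wording and the distinction between an amount of tissue and a property of it. It does not depend on the illustrative correlations.

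Its reach is limited to one mechanistic inference among 23 predictions, in the imaging arm of about 200 children. The behavioural arm, the other hypotheses and the stated sample sizes and power are unaffected. It is worth correcting before analysis because the study already plans a scan suited to the question.

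**What to change.** 1. Add a test of Hypothesis 2.2 that relates BOLD variability to the myelin-sensitive measures used for Hypotheses 2.3 and 2.4, including the MP2RAGE-derived measure. Log it as a dated change to the preregistration.
2. Keep the preregistered volume test alongside it, delete the bracketed reference to better myelination, and interpret it as a volume result only. Preferably account for head size, using the structural scan already planned.
3. In reporting, identify which of the two tests was registered first, and base any statement about myelination and neural noise on the myelin-sensitive test.

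The cost is some extra image processing and one additional, later-registered analysis. No new scan is needed, and no sample size or power figure changes.

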##### Cognitive factors

**Cognitive functioning**

Inattention has consistently been identified as a strong and specific predictor of cognitive variability, specifically variability in response times. For instance, Aristodemou et al. [19] found that higher inattention, but not hyperactivity, showed higher cognitive variability, with similar patterns observed in other studies [48, 49]. Two studies have also shown that a reduction in attentiveness as a function of time on task leads to an increase in response time variability [19, 30]. Lastly, longitudinal studies show that inattention symptoms are associated with greater cognitive variability at follow-up [50, 51].

Similar patterns are observed for the adjacent but distinct construct of mind wandering. Mind wandering reflects spontaneous changes in attention (lapses), which are related to variability (e.g., [52]), and may cause variability in cognitive performance [39]. For instance, Unsworth and Robinson [30] demonstrated that on occasions when individuals reported mind wandering, they had lower (relative) performance on working memory tasks. Conversely, individuals with lower (baseline) working memory performance, reported more frequent mind wandering. Mind wandering could be a basis for attentional lapses causing more cognitive variability, but mind wandering in turn can also be triggered by poor executive control in tasks where sustained attention is required [53].

On the other hand, it may be plausible that mind wandering plays a positive role in (long term) cognitive performance, supporting the generation and exploration of novel ideas in the creative process [54]. Mind wandering could facilitate the process of finding more remote associations to the topic, resulting in the generation of more original ideas or solutions in problem-solving [55]. In the CODEC study we further investigate such relations between mind wandering and cognitive variability.

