#### Imaging assessment

Before the imaging session in the scanner, children perform each of the five original cognitive tasks as used in the behavioural part for 3 min (15 min) and the child participants finish a set of tailored questionnaires and tasks. These are:*A digital mood scale:* a smiley question that assesses the child’s mood. The smiley changes along with the slider and ranges from an unhappy or sad smiley to a happy or joyful smiley. The number indicated by the slider ranges from 0 (unhappy smiley) to 100 (happy smiley).*A digital sleep scale*: a question that assesses the child’s sleep the evening before the session. The icon ranges from a bad night’s sleep (0) to a good night’s sleep (100).*Highly Sensitive Child scale – short form:* the HSC is a 12 item self-report scale (from 1-strongly disagree to 7-strongly agree) measuring environmental sensitivity. This scale has good internal consistency in children as young as 8 years ([109], for the Dutch version see [110]).*Mind Excessively Wandering Scale*: The MEWS is a 12 item self-report measure rating items on a scale from 0 (not at all or rarely) to 3 (nearly all of the time or constantly). The MEWS has an acceptable internal consistency in both adults and children from 8–13 years [111].*Alternative uses tasks:* children are asked to produce as many alternative uses for five physical objects (cap/hat, pen, cloth hanger, spatula, and a towel) for 2 min per object, based on Van Dijk et al. [112]. The experimenter reports the responses on a tablet, either by indicating one of the responses identified as an unoriginal answer in the study by Van Dijk et al. [112] or by writing out the answer. Fluency, flexibility, and originality are calculated.

During the imaging session, two blocks of fluid reasoning (2*8,5 min each) are performed by the child, one with low time constraints (30 s) and one with high time constraints (10 s). The time constraints are known to induce different task strategies which is a key variable of interest [66]. During the two task blocks, we record response time, accuracy, gaze direction, and pupil dilation (through the Eyelink 1000 Plus eye-tracking system). This requires a brief period of calibration (2 min) at the start of each fMRI task block.

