Optimal cognitive performance often involves finding a balance between exploring different strategies and exploiting successful ones. For instance, for a matrix reasoning task, individuals may use either elimination (ruling out response options) or constructive matching (building a prediction, and then examining whether it is among the available options, [125]). Using fMRI data, we will study whether differences in strategy use govern individual differences in variability, and whether we can identify neural networks associated with different strategies as a potential mechanism underlying trial-to-trial variability. While exploring different strategies may temporarily reduce performance, it could facilitate long-term improvement by promoting exploration and adaptation. We also use eye-tracking data to infer foci of attention and task strategies, and changes in pupil dilation during the fMRI task blocks as a proxy for fluctuations in underlying noradrenergic and dopaminergic processes.*Hypothesis 2.5: Individuals with greater variability (estimated with DSEM) will show a larger number of response strategies within the fluid reasoning task (estimated through eye tracker analysis, cf. *[66]*).**Hypothesis 2.6: Greater fMRI resting state variability (as quantified by blood oxygenation level-dependent standard deviations) is associated with better, and less variable behavioural performance in children.**Hypothesis 2.7: Different trial strategies, estimated using eye tracker analysis *[66]* will be associated with recruitment of neural networks that differ qualitatively (i.e., different centroid and negligible spatial overlap).*

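### Hypothesis 2.6 is worded as a resting-state hypothesis, but no rest run is listed: the scan carrying that label is a film clip

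*Protocol article*

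**What the plan says.** All references are to the protocol article.

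- **Key hypotheses, Aim 2.** Hypothesis 2.6 states that "Greater fMRI resting state variability (as quantified by blood oxygenation level-dependent standard deviations) is associated with better, and less variable behavioural performance" in children. It is one of the key preregistered predictions and belongs to the aim on underlying mechanisms.
- **CODEC-MRI: imaging procedure, scan list.** The one functional run outside the reasoning task is described as "Naturalistic viewing fMRI: participants will watch a short video clip (~8 min), featuring a social scene from an age-appropriate, mainstream movie".
- **Table 1.** The corresponding row is labelled "Resting-state fMRI", and its task column reads "Movie watching".
- **Imaging assessment.** The other functional data come from "two blocks of fluid reasoning (2*8,5 min each) are performed by the child". On attention-related recording, the text says: "During the two task blocks, we record response time, accuracy, gaze direction, and pupil dilation". The scan list likewise mentions eye-tracking only beside the two reasoning runs.
- **Cognitive functioning.** "Inattention has consistently been identified as a strong and specific predictor of cognitive variability, specifically variability in response times".
- **Neural factors.** BOLD variability is discussed as possibly reflecting the range of states a brain can occupy, and is said to rise with task complexity.

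**The concern.** The exposure named in the hypothesis and the data that will supply it do not match. By the article's own account in Neural factors, BOLD variability depends on the state and demand a person is under, so rest and film viewing cannot be treated as interchangeable. The hypothesis is mechanistic, so what the exposure measures decides what a positive result means. Left as it is, the study could report an association between resting-state variability and behaviour without having scanned any child at rest.

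There is a secondary issue. A film drives the signal from outside, and children may differ in how closely they follow it. The article names inattention as a predictor of behavioural variability and describes no measure of attention during the film. Attention to the film is therefore one possible alternative reading of a positive result.

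**Working it through.** **1. Is there a rest run?** Set side by side:

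| Source | Functional run | Condition |
|---|---|---|
| Scan list | Naturalistic viewing | Film clip, about 8 min |
| Scan list | Task 1 | Fluid reasoning, low or high time constraint |
| Scan list | Task 2 | Fluid reasoning, the opposite constraint |
| Table 1 | Row labelled resting-state | Movie watching |
| Table 1 | Row labelled task fMRI | Matrix reasoning |

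The structural, field-map and diffusion sequences also carry no task, but they do not yield the BOLD time series that Hypothesis 2.6 needs. The row labelled resting-state has 350 volumes at a TR of 1500 ms: 350 × 1.5 s = 525 s = 8.75 min. That matches a clip of about 8 min and leaves roughly 0.75 min over. It is the film run, with no room for a separate rest block of useful length.

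**2. The article's imaging power, reproduced.** Power ≈ Φ(atanh(r)·√(N−3) − 1.96), with N = 200 and two-sided 5% assumed because alpha is not stated. At r = 0.2 this gives 81.2%, and at r = 0.3 it gives 99.1%. The stated figures (above 80% and above 99%) hold, so this point is not about power.

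**3. How much could attention to the film matter?** Let a be the correlation of attention with film BOLD standard deviation (SD), and b the size of its association with behavioural variability. With no other link, the induced correlation has size a·b.

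- b comes from the sample size section: 0.24 for inattention and 0.53 for mind wandering. Only the magnitude is used; the article prints the latter with a negative sign.
- a is not in the documents. It is an assumption, taken here in the direction that favours the hypothesis.
- Two-sided 5% threshold at N = 200: t/√(198 + t²) with t = 1.972 gives |r| = 0.139.
- The expected correlation reaches the threshold at a = 0.139/0.24 = 0.58, or at a = 0.139/0.53 = 0.26.

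Chance of a significant result in the predicted direction from attention alone, Φ(atanh(ab)·√197 − 1.96):

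| a (assumed) | b = 0.24 | b = 0.53 |
|---|---|---|
| 0 | 2.5% | 2.5% |
| 0.2 | 10% | 32% |
| 0.3 | 17% | 61% |
| 0.5 | 40% | 97% |
| 0.6 | 53% | >99% |

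Worked example: a = 0.3, b = 0.24 gives ab = 0.072; 0.0721 × 14.04 − 1.96 = −0.95; Φ = 17%. A simulation with 4000 repetitions agrees: 17.6% and 61.1% at a = 0.3, 40.8% and 97.2% at a = 0.5. Adjusting for a perfectly measured attention score brought rejection back to about 5% (4.7% to 5.4%).

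**The case against.** **The condition is disclosed.** The scan list says naturalistic viewing and the table row says movie watching, so a careful reader can tell what was meant. That stands: nothing is hidden. It does not remove the mismatch, because the hypothesis itself, which is what will be tested and reported, still says resting state.

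**A reader might infer that attention to the film would by itself confirm the hypothesis.** The documents do not support that. They give no link between attention and film BOLD SD, and no direction for one. If inattentive children have larger fluctuations unrelated to the film, the effect shrinks or reverses. With the inattention association of 0.24, the assumed link has to be large (0.58) before the expected correlation reaches the threshold; the high percentages need the mind-wandering figure. The quoted sentence on inattention also concerns response-time variability, so it bears on only one half of a hypothesis that predicts better performance as well.

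**A variance-share argument does not settle the size either.** With the intrinsic part fixed, a child whose stimulus-locked share of variance is s has an SD higher by the factor 1/√(1−s) than a child with no locking at all: 11.8% at s = 0.20. Two children at s = 0.10 and s = 0.20 differ by only √(0.9/0.8) − 1 = 6.1%. The article gives no between-child spread of BOLD SD, so such percentages cannot be turned into a correlation.

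**Attention may belong to the mechanism.** The dynamic-range account in Neural factors includes being alert and on-task. Making a residual signal the main test might strip out part of the construct. This is a fair objection, and it is why the analysis below is a sensitivity analysis only.

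**Conclusion.** The mismatch is certain from the text: none of the three listed functional runs is at rest, and the one labelled resting-state is the film. The article does not name the run for Hypothesis 2.6, but the row label points to the film, and the only alternatives are reasoning-task runs, which are not rest either. A resting-state conclusion would therefore be unsupported whichever run is used. Hypothesis 2.2 also refers to BOLD variability without naming a run; it is affected only if it draws on the film.

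The attention explanation is a possibility, not a demonstrated bias. Its size rests entirely on the assumed a, and the table above shows only what different assumptions would imply. The stated power is unaffected. The correction is worth making before analysis because it concerns the meaning of a key preregistered hypothesis and costs very little.

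**What to change.** - State Hypothesis 2.6 as BOLD variability during movie watching, and do the same for Hypothesis 2.2 if it uses this run.
- Relabel the Table 1 row to match, and draw no conclusion about resting state.
- Keep total BOLD SD as the main measure.
- Name one sensitivity analysis in advance, on data the protocol already collects. One option is BOLD SD after removing the leave-one-out group-average time course, which is feasible if all children see the same clip. Another is adjustment for the child's Mind Excessively Wandering Scale score. That score is a trait measure and would control attention during the film only in part. Likewise, a residual from a film run is still not rest.

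The cost is a change of wording and a little extra analysis, with no new scanning. The downside is less direct comparability with earlier resting-state work.
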